### Allocation, evaluation and blindness

2.5

The choice of the surgical modality was mainly determined by the surgeon based on technical and oncological reasons. The team of surgeons who performed the surgery had performed more than 50 cases of RATS previously. It has been reported that, after surgeons had completed about 20 cases of robotic-assisted lobectomy, the operative time had been reduced significantly, and the rate of complications had stabilized, which can be considered as basic mastery of the technique, accumulating 50–90 cases of experience to achieve technical proficiency (14).

Diaphragmatic ultrasound was performed twice by 2 observers (1 independent anesthesiologist and 1 resident trainee, who were not involved in intraoperative anesthesia management) to quantify inter-observer variability, both of whom had undergone 3 months of specialized training in diaphragmatic ultrasound and were familiar with ultrasound theory and practice, using smart ultrasound instrumentation. PPCs are recorded only if two supervising physicians (who were unaware of the diaphragmatic ultrasound parameters) diagnose the same PPCs in the same patient.

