#### Operating process

2.3.1

1st day before surgery (T0), 30 min post-extubation in the Post-anesthesia Care Unit (PACU) (T1), 1st day after surgery (T2), and 3rd day after surgery (T3), diaphragmatic ultrasound was performed with the patient in a semi-recumbent position in bed with the head of the bed elevated by 30° performing quiet breathing. We recorded DE during voluntary calming respiration (7) (excluding deep inspiration and sniff manoeuver, as these two maneuvers are associated with poor compliance in postoperative patients due to pain and chest drain tube interference), we evaluated both left and right hemidiaphragms. To standardize the acoustic window across time points, preoperatively (T0) we mark the probe position on the chest wall using skin-friendly, non-irritating markers, recording the distance from the midclavicular line/anterior axillary line and rib interspace. Postoperatively, if surgical dressings, chest tubes, or subcutaneous emphysema block the original site, we adjust the probe to the nearest adjacent interspace while maintaining the same anatomical orientation relative to the diaphragm dome, documenting the adjustment in the case report form. All diaphragmatic ultrasound measurements at T0–T3 time points are performed by the same fixed team consisting of 1 experienced independent anesthesiologist and 1 resident trainee, both of whom have completed 3 months of specialized training in diaphragmatic ultrasound, to minimize inter-observer variability. The independent anesthesiologist always performed the measurements by first marking the best acoustic window on the patient’s chest for the trainee’s observation of the measurements.

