DE was assessed using a 3.5–5 Mhz convex ultrasound probe with the liver and spleen as the ultrasound windows for the right and left hemidiaphragm, respectively. To show the right hemidiaphragm, the probe was placed between the midclavicular and anterior axillary line intercostals, whereas for the left hemidiaphragm, a subcostal or low intercostal probe position was chosen between the anterior midaxillary line. For left hemidiaphragm measurement, if the splenic acoustic window is insufficient (unclear diaphragm visualization for ≥3 consecutive breathing cycles), we adjust the probe angle, increase the imaging depth (up to 6 cm), or use the left subcostal approach with the patient slightly rotated to the right. If visualization remains unsuccessful, we document the left hemidiaphragm as “unmeasurable” and focus on the right hemidiaphragm (especially the surgical side, if unilateral resection) for analysis. The hemidiaphragm probe line was selected using the two-dimensional mode (B mode). The probe was fixed to the chest wall with the ultrasound probe located medially, cephalad, and dorsally so that the ultrasound beam reached the posterior portion of the hemidiaphragm dome at an angle as close to 90 as possible, and then the ultrasonography machine was switched to the motion mode (M mode). Using anatomical M-mode (AMM), during inspiration, the normal diaphragm contracted and moved caudally toward the transducer; this was recorded as an upward movement tracked by the motion mode and was regarded as a diaphragmatic excursion during inspiration, which was measured on the vertical axis from baseline to maximum inspiratory height on the frozen image, and the resultant was the DE (Figure 3) (18, 19). Similarly, the left hemi-transverse diaphragm mobility was measured under the splenic window.

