##### Multimodal analgesia regimen

2.4.3.1

Before the end of surgery, 50 mg flurbiprofen axetil is administered intravenously. At the end of surgery, the surgeon administers intercostal nerve block (site: T3–T7, 0.2% ropivacaine with epinephrine 1:200000, 3–5 mL at each site, using repeat doses) (28); Then a patient-controlled intravenous analgesia (PCIA) pump will be installed. PCIA pump setting: background infusion condition is hydromorphone 0.002 mg/kg/h, the bolus setting is maintained at 0.002 mg/kg, the lockout interval is 10 min (29, 30). When NRS > 4, oxycodone 10-20 mg was administered intravenously to remedy analgesia, twice per day; the standard dose was 20 mg, which was reduced to 10 mg if the patient developed nausea (31). Once the patient’s pain is relieved, perform a diaphragm ultrasound examination on the same day only when NRS ≤ 4. Ondansetron is used to prevent postoperative nausea and vomiting (PONV). Postoperative pain was assessed by the same two physicians throughout the study period using an 11-point numerical rating scale (NRS 0 = no pain; 10 = worst possible pain) immediately after extubation (T1), 1st day after surgery (T2) and 3rd day after surgery (T3), respectively. Additionally, Ramsay sedation scores were performed by the same two physicians at the same time (we incorporated this score into the outcome measurement to clarify whether there is heterogeneity in postoperative sedation levels among the target population and to explore whether or how postoperative sedation levels influence diaphragmatic function or pulmonary outcomes).

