#### Primary endpoint

2.7.1

Incidence of PDD (DE values less than 10 mm or negative) at 1 day postoperatively.

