### Data collection and processing

2.10

We also recorded other parameters: age, gender, BMI, ASA classification, NYHA classification, metabolic equivalents (MET), preoperative comorbidities (COPD, chronic heart disease, chronic liver disease, metabolic disorders), pulmonary function, smoking history, Hb, SpO2, albumin, presence of respiratory infections in the previous month, ARISCAT score (33, 34), Arozullah score, surgical approach (VATS/RATS), surgical site and side, duration of surgery, extent of surgery, duration of intraoperative one-lung ventilation, amount of intraoperative rehydration and bleeding, extent of lymph node dissection, duration of postoperative chest tube drainage (to explore its potential association with diaphragmatic function), DE values during voluntary calming respiration at each time point (T0–T3), acoustic window adjustment records (if any) and left/right hemidiaphragm measurability status, duration of postoperative hospitalization and adverse events during the perioperative process. All data will be recorded in the same Excel sheet. Ultrasound images and videos will be copied from the ultrasound machine and stored on a removable hard disk for viewing.

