We emphasize the importance of performing diaphragm ultrasound in perioperative patients with thoracic surgery, a high-risk group for PPCs, to demonstrate the clinical efficacy of POCUS during the perioperative period. This includes preoperative risk stratification and early postoperative PDD detection. Establishing standardized evaluation criteria is also crucial for guiding the targeted and effective application of POCUS in perioperative care. Our pre-experiments demonstrated that DE has higher feasibility and reproducibility in the postoperative environment when used for PDD exploration. It is reported that interobserver reliability has been shown to yield a bias below 0.1 cm with limits of agreement (LOA) of ±0.3 cm for DE, compared to a bias of −2% and wider LOA of ±21% for DTF (35). Therefore, DE serves as our primary measurement metric for assessing PDD. We acknowledge that DE only recorded during voluntary calming respiration without performing and recording “Deep Inspiration” or “Sniff Maneuver” at each time point is a significant limitation. Observed diaphragmatic dysfunction based on voluntary calming respiration may be exacerbated by postoperative pain and chest tube discomfort, which leads to difficulty in distinguishing between true diaphragmatic weakness and pain-induced restricted breathing (splinting) in the early postoperative period and thus limits the ability to isolate intrinsic diaphragmatic contractility. Additionally, although a peripheral adductor hallucis train-of-four ratio ≥0.9 is the clinical gold standard for safe extubation and sugammadex is administered to reverse neuromuscular blockade, the differential recovery between peripheral muscles and the diaphragm may lead to overestimation of surgical diaphragmatic dysfunction at the T1 (30 min post-extubation) time point; this potential pharmacological noise remains a theoretical possibility that needs to be considered when interpreting early postoperative POCUS results of diaphragmatic function. However, DE is heavily influenced by paradoxical movement and chest wall mechanics after thoracic surgery, which may reflect passive displacement rather than active diaphragmatic dysfunction. In contrast, DTF directly measures diaphragmatic muscle contractility—a key physiological parameter of active function. This limitation is addressed by analyzing DTF as a complementary metric to DE, ensuring comprehensive assessment of diaphragmatic function beyond passive excursion. Furthermore, we will investigate the potential of DTF as a diaphragmatic contraction force to provide additional insights for related research. The ARISCAT score is currently the most widely used tool for assessing the risk of postoperative complications (PPCs) in surgical patients, which showed good discrimination with AUC 0.83 (95% CI 0.79–0.86) on a receiver-operating characteristics curve and the accuracy was also good with a Brier score of 0.19 (34). To demonstrate the incremental predictive value of integrating POCUS parameters with the ARISCAT score, Net Reclassification Index (NRI) and Integrated Discrimination Improvement (IDI) will be used to quantify whether the addition of diaphragmatic ultrasound indicators (e.g., DE, DTF) significantly enhances the discriminatory ability of the ARISCAT score alone. Finally, we hope to further improve the accuracy and applicability of PPCs risk stratification by combining ARISCAT score with perioperative diaphragmatic function detected by POCUS.

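### Section 2.5 states masking for the PPC assessors but not for the reading of diaphragmatic excursion (DE) that decides the 10 mm primary endpoint, although images and videos are stored

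*Protocol article*

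**What the plan says.** All references are to the protocol article.

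- **Endpoint (2.7.1):** "Incidence of PDD (DE values less than 10 mm or negative) at 1 day postoperatively".
- **Masking that is stated (2.5):** a PPC counts only if two supervising physicians agree on it, and these are physicians "who were unaware of the diaphragmatic ultrasound parameters". Section 2.4.7 says the same of PPC recording, which runs from day 1 to day 7.
- **Ultrasound observers (2.5):** one anaesthesiologist and one trainee, "who were not involved in intraoperative anesthesia management". Both scan each patient, to quantify variability between observers. Nothing is stated about masking to surgical approach, clinical state or earlier values.
- **How DE is read (2.3.1):** from the M-mode trace, "which was measured on the vertical axis from baseline to maximum inspiratory height on the frozen image". The same team scans at T0 to T3, and the senior observer marks the window for the trainee.
- **Setting (2.3.1 and 2.4.3.1):** "if surgical dressings, chest tubes, or subcutaneous emphysema block the original site, we adjust the probe to the nearest adjacent interspace"; and, after pain relief, "perform a diaphragm ultrasound examination on the same day only when NRS ≤ 4".
- **Stored material (2.10):** "Ultrasound images and videos will be copied from the ultrasound machine and stored on a removable hard disk for viewing". No measurement from these files is described.
- **Observer error (Discussion):** a cited bias below 0.1 cm, "with limits of agreement (LOA) of ±0.3 cm for DE".

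**The concern.** Masking runs in one direction. The PPC assessors cannot be influenced by the ultrasound, but nothing stated keeps the ultrasound reader from being influenced by what is visible at the bedside. Not having given the anaesthetic is separation of roles; it does not hide the approach or the patient's condition.

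The day-1 scan falls on the first day of PPC recording. An early sign, such as a low saturation needing oxygen (part of the respiratory failure definition in Table 1), could be in view while calipers are placed against a known 10 mm limit. Two observers do not remove this: duplicate readings measure scatter, and both observers share the same setting.

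Three results use the reading: the PDD incidence (primary endpoint), the VATS–RATS comparison, and the PDD–PPC association, which is part of the primary objective and the basis of the sample size. A shift common to all patients distorts the first. A shift in only some patients distorts the other two.

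**Working it through.** **1. The plan's own sample size.** Inputs from 2.8: PDD share B = 0.30, PPC share P = 0.37, OR 3.0, alpha 0.05 (taken as two-sided), power 0.80, dropout 10%.

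n = (1.960 + 0.842)² / [P(1−P) · B(1−B) · (ln 3)²] = 7.849 / (0.2331 × 0.21 × 1.207) = 132.8, so 133; 133 / 0.9 = 147.8, so 148.

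The stated 148 reproduces. The sample size is not at issue and would not change with a masked reading.

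**2. Effect of a reading shift on the PDD share.** From the article: cut-off 10 mm, PDD 30%, cited observer bias below 1 mm. Assumed: DE is roughly normal with SD 4, 5 or 6 mm. If 30% lie below 10 mm, the mean is 10 + 0.524 × SD. Reading every value d mm too low gives

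PDD share = Φ(−0.524 + d/SD), and OR = [share/(1 − share)] / (0.30/0.70).

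| SD (mm) | Mean (mm) | Share, d = 0.5 | OR | Share, d = 1 | OR |
|---|---|---|---|---|---|
| 4 | 12.1 | 34.5% | 1.23 | 39.2% | 1.50 |
| 5 | 12.6 | 33.6% | 1.18 | 37.3% | 1.39 |
| 6 | 13.1 | 33.0% | 1.15 | 36.0% | 1.31 |

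Reading 1 mm too high instead gives 21.9%, 23.4% and 24.5%. With a tighter SD of 3 mm, the 1 mm downward shift gives 42.4% (OR 1.72).

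**3. Comparison with sampling error.** The 95% half-width for 30% at n = 148 is 1.96 × √(0.21/148) = 7.4 points. A 1 mm downward shift moves the incidence by 6.0 to 9.2 points, about the same size. A 0.5 mm shift moves it by 3.0 to 4.5 points, which is smaller.

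**4. PDD–PPC association.** At OR 3.0 and 37% PPC overall, the PPC risk is 0.553 with PDD and 0.292 without. The PDD share is then 0.30 × 0.553/0.37 = 0.448 in patients with PPC and 0.30 × 0.447/0.63 = 0.213 in the rest. Shifting only the PPC patients by 1 mm raises 0.448 to 0.548, 0.528 or 0.514 (SD 4, 5, 6), and the OR from 3.0 to 4.5, 4.1 or 3.9. With no true association, the OR becomes 1.50, 1.39 or 1.31, as in step 2. These are upper limits for a 1 mm shift, because they shift every patient with a PPC. Only those already showing signs on day 1 could be affected.

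**The case against.** **The article does not say the observers were unmasked.** That is inferred from silence and the bedside setting, and reading procedures may sit in a fuller document. This stands in part. However, 2.5 takes up blindness, states it for one set of assessors, and describes the other set without it. Recognition of VATS or RATS at the bedside is also an inference: the dressings, tubes and emphysema mentioned are not tied to one approach. Nor is it stated that observers have the T0 value in front of them.

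**A reader might infer that bias is present and favours the study hypothesis.** The documents do not support this. The Introduction argues both ways on approach: robotic surgery may spare the phrenic nerve, yet gas insufflation may impair the diaphragm. An expected direction is stated only for the PDD–PPC link (Discussion), and PPCs that develop after day 1 are unknown when the day-1 reading is made.

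**A reader might also take the ±3 mm limits as room for a 2 mm bias,** which would put PDD at 42–49%. Those limits describe scatter between observers. The systematic figure beside them is below 1 mm, so 1 mm is already its upper end.

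**Existing safeguards count.** A fixed trained team, marked probe positions, duplicate readings, the pain condition and the mixed-model analysis of DE over time reduce noise or dependence on the cut-off. None of them masks the reading.

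**Re-reading is only a partial remedy.** Probe angle and choice of breath are fixed at the bedside, and the article does not say that the stored files are free of calipers. Both points stand and limit what the fix can claim.

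**Conclusion.** The point holds as a cheap improvement to the plan. As written, a threshold reading that defines the primary endpoint has no stated masking, while the outcome it is related to does. A systematic 1 mm downward shift would take PDD from 30% to about 36–39%, comparable to the sampling error at n = 148. Confined to one approach, it would produce a spurious OR of about 1.3–1.5; the same applies to patients with early PPC signs compared with the rest. At 0.5 mm the effect on incidence stays below sampling error.

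These figures rest on an assumed SD of 4–6 mm, a normal shape, and an equal shift for every patient affected. They show how sensitive the cut-off is. They do not show that a shift occurred.

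**What to change.** Amend 2.5 to state:

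- Day-1 clips are saved without calipers, stripped of identifiers and coded.
- The same two observers re-measure them offline in random order, masked to patient identity, approach, clinical course and the bedside value.
- This masked reading classifies PDD on day 1. The bedside reading is reported alongside as a sensitivity analysis. Where stored clips cannot be re-measured (for example, because calipers are burned in), the roles are reversed.
- Acquisition remains unmasked.

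Masking to time point should not be claimed if only day-1 clips are read. Mixing in all four time points would need 148 × 4 × 2 = 1,184 clips.

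**Cost:** reading time for about 148 × 2 = 296 hemidiaphragm clips, more if both observers' scans are read. No new scans, staff or patients are needed, and N stays at 148. Masking is imperfect because the readers acquired the scans, and acquisition bias remains.

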#### Assessment of PPCs

2.4.7

Postoperatively, pulmonary complications from postoperative 1st day to 7th day were recorded by a supervising physician who was unaware of the diaphragmatic ultrasound parameters. According to European Perioperative Clinical Outcome (EPCO) definitions (6), PPCs were defined as respiratory-related adverse events occurring in the postoperative period, which mainly included: respiratory tract infections, respiratory failure, pleural effusion, pulmonary atelectasis, and pneumothorax, bronchospasm, aspiration pneumonia (Table 1). In addition, PPCs were categorized as mild, moderate, or severe using pragmatic severity grading (Table 2).

**Table 1 tab1:** Postoperative pulmonary complications (PPCs).

Complications	Definition
Respiratory tract infection	The patient is receiving antibiotics for a suspected respiratory infection that meets one or more of the following criteria: new or altered sputum, new or altered cloudy lungs, fever, and a white blood cell count of >12 × 109/L
Respiratory failure	Postoperative room air inhalation PaO2 < 8 kPa (60 mmHg), PaO2: FI02 ratio < 40 kPa (300 mmHg), or arterial oxygen saturation < 90% measured by pulse oximetry, requiring oxygen therapy
Pleural effusion	Chest radiographs show blunting of the rib-diaphragm angle, loss of clear contour of the ipsilateral hemidiaphragm in the upright position, evidence of displacement of adjacent anatomical structures, or (in the supine position) blurred shadows of one hemithorax with preserved vascular shadows
Atelectasis	Lung turbidity, displacement of the mediastinum, hilar or hemidiaphragm toward the involved area, compensatory hyperinflation of the adjacent non-atelectatic lungs
Pneumothorax	Air in the pleural cavity, no vascular bed around the visceral pleura
Bronchospasm	Newly recognized expiratory wheeze treated with bronchodilators
Aspiration pneumonia	Acute lung injury following inhalation of regurgitated contents

**Table 2 tab2:** Pragmatic severity grading criteria (severity grading).

Severity	Definition	Clinical processing needs
Mildly	Causes only temporary damage and usually requires no special treatment	May require observation or basic support only (e.g., oxygen)
Moderately	More serious complications, but usually not leading to permanent damage or functional limitations	Clinical intervention required (e.g., antibiotics, noninvasive ventilation)

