### Sample size calculation

2.8

Sample size is recalculated based on the primary predictive objective (logistic regression for the association between PDD and PPCs). Based on the literature review of perioperative PPCs incidence in minimally invasive thoracic surgery (VATS/RATS) with standardized EPCO complication definitions and complete 7-day postoperative follow-up and our pilot study, the baseline PPC incidence of 37% was selected as the core assumption for this power analysis and sample size calculation; Assuming a PDD incidence of 30% postoperatively (7, 12), a PPCs incidence of 37% in the study population (1–5, 15, 32), an odds ratio (OR) of 3.0 for PDD predicting PPCs (7, 28), alpha = 0.05, power = 0.80, and 10% dropout rate, a minimum of 148 patients in total is required. Sample size estimation is performed using PASS software (PASS 15 Power Analysis and Sample Size Software (2017). NCSS, LLC. Kaysville, Utah, United States)^1^ with logistic regression parameters accounting for covariates (age, BMI, ASA classification), and the above parameter selection fully aligns with the literature review results of PPCs incidence in minimally invasive thoracic surgery, ensuring the consistency between clinical evidence and statistical methodology.

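### Sections 2.4.7 and 2.5 give contradictory rules for recording a PPC, and the 2.5 rule, read literally, drops a complication that the two physicians label differently

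*Protocol article*

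**What the plan says.** Three places in the protocol article bear on how a PPC comes to be counted.

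- **Section 2.4.7 (Assessment of PPCs):** "pulmonary complications from postoperative 1st day to 7th day were recorded by a supervising physician who was unaware of the diaphragmatic ultrasound parameters". This is one assessor. Table 1 in the same section lists seven complication types.
- **Section 2.5 (Allocation, evaluation and blindness):** "PPCs are recorded only if two supervising physicians (who were unaware of the diaphragmatic ultrasound parameters) diagnose the same PPCs in the same patient". This is two assessors, and they must agree on the same complication.
- **Section 2.8 (Sample size calculation):** "the baseline PPC incidence of 37% was selected as the core assumption for this power analysis". The figure is said to come from minimally invasive thoracic surgery literature "with standardized EPCO complication definitions and complete 7-day postoperative follow-up and our pilot study". The section does not say how many assessors stood behind either source.

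PPC incidence is a secondary endpoint (2.7.2). Its association with postoperative diaphragmatic dysfunction (PDD) is part of the primary objective (2.6.1), and that association sets the sample size (2.8).

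**The concern.** A complication named by one physician only is an event under 2.4.7 and not an event under 2.5. A reader cannot tell which rule will produce the data.

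The 2.5 rule also has a consequence that is hard to want for a composite outcome. Several Table 1 types overlap on imaging: atelectasis and pleural effusion, for example, both refer to displaced neighbouring structures. If one physician calls a picture atelectasis and the other calls it effusion, and they match on nothing else, the patient is coded as having no PPC although both saw one.

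At stake are the PDD–PPC model that fixes the sample size, and the analyses in 2.9 that use PPC as outcome: the risk-factor regression with its ten-events-per-variable limit, the ROC analysis, and the NRI and IDI comparisons. The primary endpoint, PDD on day 1, is not affected.

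**Working it through.** **1. The plan's own figure.** Inputs from 2.8: PDD share B = 0.30, overall PPC rate 0.37, OR 3.0, alpha 0.05 (taken as two-sided), power 0.80, dropout 10%.

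Solving 0.70·p0 + 0.30·p1 = 0.37 with an odds ratio of 3 gives p0 = 0.2917 (no PDD) and p1 = 0.5527 (PDD). With the Wald variance for logistic regression on a binary covariate:

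- V = 1/(B·p1(1−p1)) + 1/((1−B)·p0(1−p0)) = 13.48 + 6.91 = 20.40
- n = (1.960 + 0.842)² · V / (ln 3)² = 7.849 × 20.40 / 1.207 ≈ 132.6, rounded up to 133
- 133 / 0.90 = 147.8, rounded up to 148, which matches the plan. Power at 133 is 0.801, with 133 × 0.37 ≈ 49 events.

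**2. What follows without any assumption.** The patients recorded when both physicians must agree are a subset of those recorded by either one. The both-agree count therefore cannot exceed either physician's own count. This fixes the direction relative to one assessor. It does not fix the direction relative to 37%.

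**3. Illustration.** The documents give no agreement rate, sensitivity or specificity, so these are assumed. Each physician has sensitivity Se and specificity Sp for any PPC, errors are independent and unrelated to PDD, and the true rate (37%) and OR (3) are as planned.

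- One assessor: S = Se, F = 1 − Sp
- Both must agree: S = Se², F = (1 − Sp)²
- Recorded risk in each group: p′ = p·S + (1 − p)·F
- Power = Φ(ln OR′ · √(133/V′) − 1.96)

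Example, 0.90/0.90, both agree: p0′ = 0.2917 × 0.81 + 0.7083 × 0.01 = 0.243; p1′ = 0.5527 × 0.81 + 0.4473 × 0.01 = 0.452; OR′ = (0.452/0.548)/(0.243/0.757) = 2.57.

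| Se / Sp | One assessor: rate, OR, power | Both agree: rate, OR, power |
|---|---|---|
| 0.95 / 1.00 | 35.2%, 2.88, 0.77 | 33.4%, 2.78, 0.74 |
| 0.90 / 1.00 | 33.3%, 2.78, 0.74 | 30.0%, 2.62, 0.67 |
| 0.80 / 1.00 | 29.6%, 2.60, 0.66 | 23.7%, 2.38, 0.53 |
| 0.95 / 0.95 | 38.3%, 2.66, 0.71 | 33.6%, 2.77, 0.73 |
| 0.90 / 0.95 | 36.5%, 2.55, 0.67 | 30.1%, 2.61, 0.67 |
| 0.90 / 0.90 | 39.6%, 2.37, 0.61 | 30.6%, 2.57, 0.66 |
| 0.80 / 0.95 | 32.8%, 2.36, 0.59 | 23.8%, 2.37, 0.53 |
| 0.80 / 0.90 | 35.9%, 2.17, 0.51 | 24.3%, 2.32, 0.52 |

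**4. Reading the table.** The recorded rate is always lower under the both-agree rule. The odds ratio is attenuated more than with one assessor only in the perfect-specificity rows; in the others the rule removes false positives and the odds ratio is attenuated slightly less. Power moves either way. Events under the both-agree rule run from about 32 (133 × 0.237) to 45 (133 × 0.336), against 49 planned. Under the ten-events rule that supports three or four candidate variables, against four.

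The table models error on whether any PPC is present. It does not model label mismatches, on which the documents give nothing to calculate from.

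**The case against.** Requiring two blinded physicians to concur is a recognised way to favour specificity, and several Table 1 definitions are subjective enough to justify it. That stands: as the table shows, dual confirmation can give more power than one assessor. A condensed article may also leave adjudication details, such as agreement statistics, to a fuller protocol, so their absence is not a fault here. What does not fall under that allowance is a rule the article states in two incompatible ways, or the stated condition that the diagnoses must be the same.

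A reader might infer more than the documents support:

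- **That the two physicians work independently, so sensitivity is squared.** Section 2.5 does not say so. If they assess together, the calculation in step 3 does not apply.
- **That every disagreement becomes a negative patient.** The condition works per complication. A patient with one agreed PPC remains a case whatever else is disputed.
- **That the rate must fall below 37%.** Section 2.8 rests that figure partly on the authors' pilot, whose assessor rule is not given. If the pilot used the two-physician rule, there may be no shortfall.
- **That the rule weakens the PDD odds ratio and costs power relative to one assessor.** This holds throughout only if specificity is perfect, which assumes away the reason for dual confirmation.

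**Conclusion.** The contradiction between 2.4.7 and 2.5 is certain and concerns the outcome on which the sample size rests. It is equally certain that the 2.5 wording leaves an unmatched diagnosis unrecorded, and that it cannot record more events than either physician alone.

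The size of the effect is not determined by the documents. Over the assumed range (sensitivity 0.80 to 0.95, specificity 0.90 to 1.00, independent errors, true rate 37%, true OR 3, 133 evaluable patients), the both-agree rule records PPCs in about 24% to 34% of patients, with power of about 0.52 to 0.74 against 0.80 planned. These figures are not a forecast. A single imperfect assessor also falls short of 0.80 in every row, so the gap to 0.80 reflects outcome misclassification in general and cannot be charged to the agreement rule alone. It also presumes that 37% and OR 3 are error-free values.

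The text should be corrected. The documents do not support a claim that the study is underpowered for this reason.

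**What to change.** State one rule, in the same words, in 2.4.7 and 2.5:

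- Two physicians blind to the ultrasound assess each patient against Table 1.
- Unmatched diagnoses are settled by their joint review, still blind to ultrasound.
- A patient has a PPC if at least one Table 1 event is confirmed at that review, even where the initial labels differed.

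This keeps the protection against false positives and stops a confirmed complication being lost over its name. In 2.8, state whether the 37% was obtained under that rule; if it was not, say so beside the assumption.

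The cost is wording in three sections and a short review by the same two physicians, with no extra staff. Reporting kappa and a sensitivity analysis that counts a PPC named by either physician would be useful but is optional.
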